##### Tertiary Outcomes

The following tertiary outcomes will be measured with validated self-reported questionnaires that participants will fill in through online forms: **1/ Sleep:** Participants will complete the Pittsburgh Sleep Quality Index (PSQI) and the Berlin Questionnaire. PSQI scores range from 0 to 21, a lower score indicating better sleep quality. The Berlin Questionnaire will determine the risk of sleep apnea. **2/ Anxiety/mood:** The Geriatric Depression Scale (GDS), the Perceived Stress Scale, the SF-12 (quality of life), the State-Trait Anxiety Inventory, the Anxiety Sensitivity Index, the Intolerance of Uncertainty scale, the Perceived vulnerability to disease, the Connor-Davidson Resilience Scale 10, and the Perseverative Thinking Questionnaire, will be used to assess mood and anxiety. **3/ Cognitive reserve:** will be evaluated at baseline. To do so, participants will provide their total years of education and will complete a modified version of the Rami and colleague's cognitive reserve questionnaire (33), adapted for French and English by the CIMA-Q team (17, 34). **4/ Social support:** Social and Community Involvement Questionnaire (35) and the Lubben Social Network Scale will be completed. **5/ Diet:** Participants will complete the Short Diet Questionnaire (36). **6/ Prior physical activity:** Participants will fill in the Physical Activity Scale for the Elderly (37). **7/ COVID-19 impact:** The QCOVID questionnaire will be completed at baseline only. **8/ Gender:** The Bem Sex-Role Inventory will be filled at baseline only. All questionnaires will be filled in by participants using anonymous online forms.

##### Research Plan

Following the preliminary call, five videoconference sessions will be scheduled with the participants. The first session will be a technology tutorial that will ensure that internet connectivity and tools are ready and mastered enough by participants to engage in testing. Then, participants will complete 4 pre-testing sessions (T0), 4 mid-testing sessions (T1 at 3 months), 4 post-testing sessions (T2 at 6 months), and 4 optional follow-up sessions (T3 at 12 months). Total participation in this study is expected to be of a 12-month duration, including 6 months of intervention (Figure 1).

### Data Analysis

#### Sample Size Calculation

The team of biostatisticians from the Montreal Health Innovations Coordinating Centre (MHICC) performed the sample size calculation on the primary outcome, i.e., the differential effect of physical exercise training alone vs. the combined physical and cognitive training on cognitive performance (executive functions). The calculation was based on existing values available in the literature for physical exercise training alone, as well as on different plausible effect sizes for the combined physical and cognitive training (no existing values in the literature for this group), and on clinically relevant effect sizes. The calculation revealed that a sample size of 49 subjects in each group will have 80% power to detect a difference in means of−0.186 (difference between physical training alone mean of 0.239 and combined training mean of 0.425, for an effect size of 0.624), assuming that the common standard deviation is 0.325 (slightly larger than in a traditional context because of the home-based administration of neuropsychological tests) using a two-group *t*-test (0.050 two-sided significance level). As we expect a 20% attrition rate based on our previous exercise studies, we will thus recruit 61 participants per intervention arm, for a total of 122 patients with CVD. Participants will be randomized in one of the 2 arms: home-based physical training alone or combined physical and cognitive home-based training. A biostatistician from the MHICC generated the randomization sequence.

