## Abstract

**Introduction:** During the COVID-19 pandemic, confinement measures are likely to produce collateral damage to health (stress, confusion, anxiety), especially in frail individuals and those living with cardiovascular disease (CVD). In cardiac patients in particular, these measures dramatically increase the level of physical inactivity and sedentary lifestyle, which can decrease cardiorespiratory capacity and increase the risk of acute events, rehospitalization, and depressive syndromes. Maintaining a minimum level of physical activity and cognitive stimulation during the COVID-19 crisis is essential for cardiac patients. This study is designed to document the effects of 6 months of home-based physical exercise alone or combined with cognitive training on cognitive and physical functions in patients with CVD over 50 years old.

**Methods and Analysis:** 122 patients (>50 years old) with stable CVD and no contraindication to perform physical exercise training will be recruited and randomly assigned to one of the 2 following arms: (1) Home-based physical exercise alone, (2) Home-based physical exercise combined with cognitive training. The intervention lasts 6 months, with remote assessments performed prior to, mid and post-training. A follow-up 6 months after the end of the intervention (12 month) is also proposed. The primary outcome is cognition, including general functioning (Montreal Cognitive Assessment (MoCA) score), as well as performances on measures of executive functions, processing speed, and episodic memory. The secondary outcome is physical performance, including balance, gait and mobility, leg muscle strength and estimated cardiorespiratory fitness. Tertiary outcomes include mood, anxiety, and health-related quality of life as assessed by self-reported online questionnaires.

**Discussion:** With the COVID-19 crisis, there is a critical need for remote exercise and cognitive training, and to further investigate this topic, in particular for cardiac patients. The present context can be viewed as an opportunity to perform a major shift from center-based programs to home-based physical exercise. This is especially important to reach out to older adults living in remote areas, where access to such interventions is limited.

**ClinicalTrials.gov:** [https://clinicaltrials.gov/ct2/show/NCT04661189], NCT04661189.

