##### Primary Outcome: Cognitive Performances

The primary outcome of the study will be cognitive performances. Participants will be tested for general cognitive functioning using a remote version of the Montreal Cognitive Assessment (MoCA) (24). Also, three main components of cognition will be assessed with a comprehensive neuropsychological evaluation, from which composite z-scores will be computed: executive functions, processing speed and episodic memory. The neuropsychological assessment will include the following tests that will be administered in a predetermined order: Rey auditory verbal learning test, Digit Span, oral Trail Making Test (25), Phonological and Semantic Fluency from the D-KEFS battery (26), and Similarities subtest from the WAIS-IV (27). The neuropsychological assessment, including the MoCA, will be performed via videoconference (Zoom). All tests have been validated for remote administration and have previously been used in large participant cohorts (28). Importantly, these tests are validated and normed for an older adult population (17, 21, 29). The similarities subtest will only be completed at baseline to obtain a measure of crystallized intelligence; its completion will be optional and performed according to participant's fatigue. Participants will also realize a computerized or tablet-based cognitive assessment (30). The three computerized cognitive tasks include a dual-task (30), Stroop task, and N-back. Participants will complete trained and transfer versions (same tasks but with different stimuli) that will be presented in a counterbalanced order between participants, via a latin-square procedure. Comparing trained and transfer tasks allows to quantify participants' ability to transfer cognitive training effects to novel tasks. Subcomponents of each task allow dissociating different attentional control mechanisms from mere cognitive speed. Importantly, the tasks record response time in milliseconds, which reduces the likelihood of ceiling effects. These tasks also tend to be more sensitive to training effects. Finally, computer equipment (i.e., computer or tablet) used by participants for the computerized tasks will be documented. Participants will be asked to use the same computer equipment for the four testing periods (including the 12-month follow up).

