#### Statistical Analysis

The variables in the study will be presented using descriptive statistics. The mean, standard deviation, median, minimum, Q1, Q3 and maximum will be presented for continuous variables. The number and percentage will be presented for nominal/ordinal variables. The assumptions of the statistical tests will be examined, and data transformation or non-parametric analyses may be used as appropriate. SPSS and SAS software version 9.4 or higher will be used to conduct the analyses.

Mean changes in cognitive performance from baseline will be analyzed using a repeated measures analysis of covariance (ANCOVA) model, adjusted for age, sex, education, including the effects of the intervention as between-subject variable (physical exercise alone or combined with cognitive training) and time as within-subject variable (pre at baseline, mid at 3 months, post-intervention at 6 months). Observation of a statistically significant difference in the primary outcome between pre- and post-intervention timepoints will be considered as the evidence of the intervention's efficacy (i.e., primary hypothesis). The interaction between intervention arms (i.e., physical exercise alone or combined training) and performance changes from pre to post-intervention will address the added value of cognitive training compared to physical exercise alone (i.e., secondary hypothesis). Secondary and exploratory outcomes will be analyzed as the primary outcome.

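### The sample-size section and the analysis section contradict each other on what is primary: the powered between-arm contrast in executive functions is ranked as the secondary hypothesis, on one of at least four unranked cognitive measures

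*Protocol article*

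**What the plan says.** All references are to the protocol article.

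- **Sample Size Calculation.** The section reports "the sample size calculation on the primary outcome, i.e., the differential effect of physical exercise training alone vs. the combined" intervention, with executive functions given as the measure. The test is a two-group t-test at the "0.050 two-sided significance level", and "a sample size of 49 subjects in each group will have 80% power". The planning values are a "difference between physical training alone mean of 0.239 and combined training mean of 0.425, for an effect size of 0.624", with a common SD of 0.325.
- **Statistical Analysis.** A significant difference between the pre- and post-intervention timepoints is the evidence of efficacy and is labelled the primary hypothesis. The interaction of arm with pre-to-post change "will address the added value of cognitive training compared to physical exercise alone (i.e., secondary hypothesis").
- **Introduction, hypotheses.** The order is the same: improvement after home-based exercise first, greater improvement in the combined arm second.
- **Abstract.** "The primary outcome is cognition, including general functioning (Montreal Cognitive Assessment (MoCA) score), as well as performances on measures of executive functions". Two further domains complete that list: episodic memory and processing speed.
- **Primary Outcome: Cognitive Performances.** The MoCA is measured, and "composite z-scores will be computed: executive functions, processing speed and episodic memory". Three computerised tasks, in trained and transfer versions, are described under the same heading. The measures are not ranked.
- **Study Limitations.** There is no control group without intervention.

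**The concern.** The contrast that fixed the sample size is primary in one section and secondary in the next, and both labels cannot stand. The outcome differs too: one domain in the sample-size section, at least four measures in the Abstract and the primary-outcome section.

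Two things are at stake. First, the analysis section's efficacy criterion is not a randomised comparison. Both arms receive exercise, neither is untreated, and the same cognitive domains are tested at baseline, 3 and 6 months. A rise from baseline to 6 months may reflect exercise, practice on the tests or the passage of time. Followed as written, the trial could declare efficacy on its primary hypothesis with no difference between the arms. Second, with no ranking among the measures, the document does not settle which result decides the primary question.

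**Working it through.** **Step 1. Reproduce the stated sample size.** Inputs from Sample Size Calculation: means 0.239 and 0.425, SD 0.325, two-sided 0.05, power 80%, two-group t-test.

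- Difference: 0.425 − 0.239 = 0.186.
- Standardised effect: d = 0.186 / 0.325 = 0.572.
- Two-sample t-test (noncentral t): n = 48.9, so 49 per arm. Power at 49 per arm is 80.1%.

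The stated 49 is reproduced, so the 80% belongs to this between-arm test on executive functions.

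The stated effect size of 0.624 does not match these inputs. It would imply an SD of 0.186 / 0.624 = 0.298, would need 42 per arm, and would give 86% power at 49. The planned n follows from 0.572.

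**Step 2. Set the sections side by side.**

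| Section | Primary contrast | Primary measure |
|---|---|---|
| Sample Size Calculation | Between arms | Executive functions |
| Statistical Analysis | Pre to post; arm interaction is secondary | The primary outcome, not specified further |
| Introduction, hypotheses | Pre to post listed first, arms second | Cognition, larger gains expected in executive functions |
| Abstract; Primary Outcome | None stated | MoCA and three domains |

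The 80% therefore describes the second row's secondary hypothesis, on one of at least four measures.

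**Step 3. Does the mismatch leave the pre-post test short of power?** Assume the two planning means are changes from baseline, 0.325 is the SD of change, and the pre-post test is taken over both arms.

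- Mean change with equal arms: (0.239 + 0.425) / 2 = 0.332.
- Standardised change: 0.332 / 0.325 = 1.02.
- One-sample t-test, two-sided 0.05, 80% power: n = 9.6, so about 10 patients.

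With 2 × 49 = 98 evaluable patients the test has ample power on this measure. It also follows that 49 per arm was not derived from it.

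**Step 4. Illustration of several measures.** Assume, since the article states no such rule, that success on any one of four measures at 0.05 each would count.

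- Independent measures: 1 − 0.95⁴ = 0.185, or 18.5%.
- Equal correlation of 0.5 (assumed; simulated): about 16%.
- Bonferroni split (assumed; the article names no method): 0.05 / 4 = 0.0125. Power at 49 per arm with d = 0.572 falls from 80% to 61%. With the stated 0.624 it would be 71%.

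**The case against.** The article condenses a fuller protocol, and a statistical analysis plan may exist. Rules for multiplicity usually belong there, so silence on adjustment is not a fault. That stands. A reader might infer that several primary tests will each be run at an unadjusted 0.05 and that the family-wise error rate is inflated. The documents do not support this: the only alpha given is the input to the sample-size test, the analysis section speaks of one primary outcome, and no rule says that any one measure suffices. Nor should the computerised tasks be counted as six further primary tests because they share a heading. They are described as measuring transfer and separating attentional mechanisms.

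A reader might also infer that the primary analysis is underpowered. Step 3 shows the reverse for the pre-post test on executive functions: the trial is sized on the more demanding contrast.

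It would also be too strong to say that nothing is named as primary. The sample-size section names one contrast and one domain, and the analysis section names one contrast. They disagree. Because the Introduction ranks the hypotheses as the analysis section does, the sponsor could argue that only the label in the sample-size section is wrong. That would remove the contradiction in wording. It would still leave an uncontrolled before-after change as the efficacy criterion, the randomised comparison in second place, and the measures unranked.

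**Conclusion.** The contradiction stands on the text alone, and an analysis plan not shown here cannot remove it from the article. The planned 80% power applies to the between-arm difference in executive functions, which the analysis section ranks second. The criterion ranked first cannot be attributed to the intervention, because no group goes without it. This should be corrected before results are known, since the article does not say consistently which result answers the primary question.

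The between-arm arithmetic rests only on the article's means and SD. The figure of about 10 patients assumes that those values are changes and the SD of change. The 16% to 18.5% and the 61% are illustrations under an assumed any-one-of-four rule, with an assumed correlation for the lower error rate and an assumed Bonferroni split for the power. They are not properties of the plan as written.

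**What to change.** - Name one primary estimand: the between-arm difference in change from baseline to 6 months in the executive-function composite, tested at two-sided 0.05.
- In Statistical Analysis, relabel the arm interaction as the primary hypothesis and the pooled pre-to-post change as secondary and descriptive. Align the order of the hypotheses in the Introduction.
- Make the MoCA, processing speed, episodic memory and the computerised tasks secondary in the Abstract and the primary-outcome section.
- Correct the effect size in Sample Size Calculation to match its inputs (0.186 / 0.325 = 0.572), or correct the inputs.

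The cost is that the other cognitive measures and the pre-post change lose any primary claim. Trial Status reports that recruitment started in May 2020, so this is a mid-trial change to the primary outcome and hypothesis. It needs a dated, justified amendment made before unblinding. No patients or data are added: 49 evaluable per arm, 80% power and N = 122 remain as planned.

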#### Statistical Analysis

The variables in the study will be presented using descriptive statistics. The mean, standard deviation, median, minimum, Q1, Q3 and maximum will be presented for continuous variables. The number and percentage will be presented for nominal/ordinal variables. The assumptions of the statistical tests will be examined, and data transformation or non-parametric analyses may be used as appropriate. SPSS and SAS software version 9.4 or higher will be used to conduct the analyses.

Mean changes in cognitive performance from baseline will be analyzed using a repeated measures analysis of covariance (ANCOVA) model, adjusted for age, sex, education, including the effects of the intervention as between-subject variable (physical exercise alone or combined with cognitive training) and time as within-subject variable (pre at baseline, mid at 3 months, post-intervention at 6 months). Observation of a statistically significant difference in the primary outcome between pre- and post-intervention timepoints will be considered as the evidence of the intervention's efficacy (i.e., primary hypothesis). The interaction between intervention arms (i.e., physical exercise alone or combined training) and performance changes from pre to post-intervention will address the added value of cognitive training compared to physical exercise alone (i.e., secondary hypothesis). Secondary and exploratory outcomes will be analyzed as the primary outcome.

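### The primary cognitive model takes change from baseline as its response while keeping baseline as a level of time, and it does not adjust for the baseline score, so available precision is given up

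*Protocol article*

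**What the plan says.** In the Statistical Analysis section of the protocol article, the cognitive outcome is handled as follows: "Mean changes in cognitive performance from baseline will be analyzed using a repeated measures analysis of covariance (ANCOVA) model, adjusted for age, sex, education". Arm is the between-subject factor, and the other factor is "time as within-subject variable (pre at baseline, mid at 3 months, post-intervention at 6 months". The list of adjustment variables ends with education; the baseline cognitive score is not on it.

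Two tests are drawn from this model. The pre-to-post difference serves the primary hypothesis. The added value of cognitive training is the secondary hypothesis, tested by "The interaction between intervention arms (i.e., physical exercise alone or combined training) and performance changes from pre to post-intervention".

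On software the section says only that "SPSS and SAS software version 9.4 or higher will be used to conduct the analyses". It names no fitting procedure and gives no rule for missed visits.

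The Sample Size Calculation section uses an unadjusted two-group t-test at a two-sided 0.05 level: "a sample size of 49 subjects in each group will have 80% power to detect a difference in means" of 0.186 (0.425 minus 0.239), "assuming that the common standard deviation is 0.325".

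**The concern.** There are two linked problems in the stated model.

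1. **The response and the time factor do not fit together.** Change from baseline is zero at baseline by construction, so baseline cannot be a level of time in a model of changes. Scores at three visits and changes at two visits are different models, and two analysts working from this text could fit different ones.

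2. **The baseline score is not used for adjustment.** With scores at three visits, the arm-by-time contrast from baseline to 6 months is the difference between arms in mean change. Age, sex and education as main effects take the same value at every visit, so they cancel from that contrast and do not stand in for the baseline score. With changes at two visits, the three covariates do enter, but the baseline score is still absent.

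At stake are the precision of the arm comparison, on which the trial was sized, and its exposure to a chance difference between arms at baseline. The baseline assessment is done before randomisation, so the information is already there.

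**Working it through.** **Inputs from the Sample Size Calculation section:** difference 0.186, SD 0.325, 49 evaluable per arm, two-sided alpha 0.05, 20% attrition, 61 recruited per arm.

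**Assumptions that the protocol article does not give:** 0.325 is the SD of the change from baseline; the variance of the score is the same at each visit; rho is the correlation between the baseline and 6-month scores, shown from 0.5 to 0.9. Whatever age, sex and education explain is left out on both sides of the comparison.

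**Step 1: reproduce the plan's figure.** The standard error of the difference is 0.325 × √(2/49) = 0.0657. The noncentrality is 0.186/0.0657 = 2.83 on 96 degrees of freedom, and the exact power of the t-test is 0.801. The stated 49 per arm at 80% is reproduced. For attrition, 49/0.8 = 61.25 against 61 stated, a rounding difference.

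**Step 2: effect of baseline adjustment on variance.** With score variance σ²:
- variance of the change: 2σ²(1 − rho)
- residual variance after adjusting for baseline: σ²(1 − rho²)
- ratio: (1 − rho²) / [2(1 − rho)] = (1 + rho)/2

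**Step 3: power at 49 per arm with SD = 0.325 × √[(1 + rho)/2].**

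| rho | variance ratio | effective SD | power at 49 per arm | evaluable per arm for 80% |
|---|---|---|---|---|
| as planned | 1.00 | 0.325 | 80% | 49 |
| 0.5 | 0.75 | 0.2815 | 90% | 37 |
| 0.6 | 0.80 | 0.2907 | 88% | 40 |
| 0.7 | 0.85 | 0.2996 | 86% | 42 |
| 0.8 | 0.90 | 0.3083 | 84% | 45 |
| 0.9 | 0.95 | 0.3168 | 82% | 47 |

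**Step 4: the alternative with a common baseline mean.** Take 61 per arm, of whom 49 have all visits and 12 have baseline only, with known compound-symmetric covariance and a normal approximation. A model of all three visits that constrains the arms to one baseline mean gives power of about 0.91, 0.87 and 0.85 at rho 0.5, 0.7 and 0.8. That is within about a point of the table, so either form recovers the precision.

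**Step 5: chance imbalance.** A baseline difference of one standard error is √(2/49) = 0.20 SD of the score. It moves the change-score estimate by (1 − rho) times that difference. Since σ = 0.325/√[2(1 − rho)], the shift equals 0.0657 × √[(1 − rho)/2]. This is 0.033 at rho 0.5 and 0.015 at rho 0.9, or about 18% and 8% of 0.186. Over repeated randomisations these shifts average to zero; in a single trial, baseline adjustment removes them.

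**The case against.** The strongest defence is that the first problem is wording. With scores at three visits as the response, baseline as a level of time is standard and the arm-by-time interaction is coherent. Baseline cannot then also be an ordinary covariate, because it is part of the response. Under randomisation the change-score comparison is unbiased, and the trial was sized on an unadjusted test, so its 80% does not depend on baseline adjustment. All of this stands. It limits the point to an ambiguity and forgone precision. It does not remove the point: the text still allows two models, and a common baseline mean uses the baseline information without making it a covariate.

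A reader might infer more in three places, and the article does not support it:

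- **Missed visits.** The plan writes "As we expect a 20% attrition rate based on our previous exercise studies", and a classical repeated-measures general linear model would discard anyone missing a visit. But that sentence only inflates the sample size. No complete-case rule or procedure is stated, and both named packages can fit models that keep partial records. Missing-data rules are commonly left to the statistical analysis plan, so their absence from an article is no finding.
- **Dropout bias.** This would need listwise deletion together with dropout related to outcome. The article states neither.
- **Time effect tested at age zero.** This would need covariate-by-time terms, uncentred covariates and a test read at the origin. The article specifies no such terms.

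**Conclusion.** The point holds as an inconsistency in the stated response and as an avoidable loss of efficiency. The described model can be read as a valid one, the arm comparison is unbiased on average under randomisation, and the planned 80% power reproduces and is met.

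The size depends on a correlation that the documents do not give. At 49 per arm the forgone power runs from about 2 points (rho 0.9) to about 10 points (rho 0.5). The variance ratio (1 + rho)/2 needs only equal variances over time; the power figures also need 0.325 to be the SD of change. The gain would be smaller to the extent that age, sex and education already explain change in the model as fitted.

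Listwise deletion would be a risk only if a classical repeated-measures general linear model were used, which the article does not say.

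**What to change.** State the response, and use one of these two forms:

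- model the 3- and 6-month changes (or scores), with arm, visit, arm-by-visit, baseline score and baseline-by-visit, in addition to age, sex and education; or
- model the scores at baseline, 3 and 6 months with a common baseline mean across arms, retaining age, sex and education.

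Fit it as a likelihood-based repeated-measures model. SAS and SPSS both support this, and it also keeps participants with partial follow-up, so naming it settles the missed-visit question.

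Keep both tests that the plan already defines: the pre-to-6-month change, estimated at the covariate means, for the primary hypothesis; and the arm difference at 6 months for the added value of cognitive training. The change of model should not replace the first with the second.

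The cost is a few sentences in the protocol or analysis plan and standard mixed-model code. No extra data, visits or participants are needed, and the sample size can stay as it is.

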
The COVEPICARDIO project will investigate the effects of home-based physical exercise with or without cognitive training, on cognitive and physical functions in older women and men with stable CVD.

Hypotheses: 1/ After 6 months of home-based physical exercise, cardiac patients will show an improvement in cognitive (primary outcome) and physical measures (secondary outcomes), with larger gains in executive functions. 2/ Cardiac patients randomized in the combined home-based physical exercise and cognitive training group will show greater improvements in cognition and physical functions post-intervention compared to cardiac patients who did not complete the cognitive training.

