### Study Limitations

Some limitations of our trial need to be mentioned. First, our design does not include a control group without intervention. Because of the pandemic context, some ethical considerations refrained the research team from implementing a control group without any intervention. However, to partially address this limitation, in our analysis we will take into account the dose response effect as a function of the volume of training performed by participants. Based on the nature of each activity, its intensity and its frequency, a weekly dose of physical exercise (converted in kcal and in METs using the Compendium of Physical Activities) will be computed. The effect of physical exercise dose on cognitive and physical functions will be evaluated according to participant's mean weekly dose during the 6 months of intervention. Based on the overall study sample distribution, participants could be classified into “higher,” “medium,” and “lower” doses of physical exercise (i.e., tercile split).

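### A significant pre-to-post change is taken as proof of efficacy although no arm is untreated, so retest gain alone could satisfy the primary hypothesis

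*Protocol article*

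**What the plan says.** The Introduction gives two hypotheses. The first is a change within patients: "After 6 months of home-based physical exercise, cardiac patients will show an improvement in cognitive (primary outcome) and physical measures". The second is that the combined arm gains more than the exercise-alone arm.

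The Statistical Analysis section attaches a decision rule to each. For the first, the rule is that a "statistically significant difference in the primary outcome between pre- and post-intervention timepoints will be considered as the evidence of" efficacy; the section labels this its primary hypothesis. For the second, the interaction of arm with pre-to-post change "will address the added value of cognitive training compared to physical exercise alone (i.e., secondary hypothesis").

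Two other sections bear on this:

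- **Study Limitations** concedes that "our design does not include a control group without intervention". It offers one partial remedy: "to partially address this limitation, in our analysis we will take into account the dose response effect as a function of the volume of training".
- **Sample Size Calculation** names the difference between exercise alone and combined training, on executive functions, as the primary outcome and sizes the trial on it.

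The Research Plan sets the testing load before the 6-month result is read: "4 pre-testing sessions (T0), 4 mid-testing sessions (T1 at 3 months), 4 post-testing sessions (T2 at 6 months").

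**The concern.** Randomisation protects the comparison between arms. It does not protect the comparison of 6 months with baseline. Because everyone exercises, the main effect of time adds together any benefit of exercise, learning from repeated testing, and anything else that changed over those months. The article mentions no alternate forms and no retest correction for the neuropsychological battery. The transfer versions of the computerised tasks are there to measure transfer of training, not to remove retest gain.

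The rule nevertheless turns a significant time effect into a finding of efficacy and makes it the primary conclusion. A programme with no effect on cognition could be reported as effective. Meanwhile the one contrast that the design can support, and for which the sample size was calculated, is ranked second.

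**Working it through.** **Inputs from the Sample Size Calculation.** Means 0.239 (exercise alone) and 0.425 (combined), difference 0.186, common SD 0.325, two-sided 0.05, two-group t-test, 49 per group for 80% power, 20% attrition, 61 per arm.

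**Reproducing the plan's figure.** Standardised difference = 0.186/0.325 = 0.572. With the noncentral t distribution, 49 per group gives power 0.801, so the 49 reproduces. Attrition: 49/0.8 = 61.25, against 61 stated. The printed effect size of 0.624 does not match 0.572. It would need an SD of 0.186/0.624 = 0.298. This does not affect the present point, but 0.298 is carried below as a sensitivity value. The calculation concerns the between-arm difference only; no figure in the article was computed for the pre-to-post rule.

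**The pre-to-post rule when exercise does nothing.** Assumptions: 2 × 49 = 98 completers; 0.325 is the SD of the change score; no true effect in either arm; the same retest gain g in both arms; the time effect approximated by a one-sample t-test on change. The article gives no value for g, so a range is shown.

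- Standard error = 0.325/√98 = 0.0328.
- Smallest mean change reaching p < 0.05 = 1.985 × 0.0328 = 0.065, which is 0.065/0.239 = 27% of the planning mean for exercise alone.
- Noncentrality = g/0.0328, that is 1.52, 3.05 and 4.57 for g = 0.05, 0.10 and 0.15.

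| Retest gain g, no true benefit | Chance that the rule declares efficacy |
|---|---|
| 0 | 5% |
| 0.05 | 33% |
| 0.10 | 85% |
| 0.15 | over 99% |

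A gain of 0.093 is enough for an 80% chance.

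**Sensitivity at g = 0.10.**

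| Completers | Change SD | Chance that the rule declares efficacy |
|---|---|---|
| 98 | 0.298 | 91% |
| 98 | 0.325 | 85% |
| 98 | 0.46 | 57% |
| 49 (one arm alone) | 0.325 | 56% |

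The article calls 0.325 a common SD without saying of what. If it is the SD at a single time point, the change SD is 0.325 × √(2(1 − r)), where r is the pre-post correlation. That gives 0.325 at r = 0.5 and 0.46 at r = 0. The 0.46 row is therefore the least favourable case for any non-negative correlation.

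**The randomised contrast under the same conditions.** In 40,000 simulated trials with equal gain in both arms, the between-arm test was significant in 4.9%, 5.1% and 5.0% of trials at g = 0, 0.10 and 0.20. The pre-to-post rule was met in 5.0%, 85.5% and 100%. Equal gain is least secure for the computerised tasks, where "Participants will complete trained and transfer versions (same tasks but with different stimuli") and only the combined arm trains on them.

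**The case against.** The authors disclose the missing control group and propose a dose-response analysis. This deserves credit: a retest gain shared by everyone would largely cancel when terciles of exercise dose are compared. But dose is chosen by the participant and self-reported, so the comparison is not randomised, and the authors themselves call it a partial answer. The efficacy rule does not depend on it either.

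The arm-by-time test is planned, powered and valid for the added value of cognitive training. That stands: the fault lies in how the time effect is read, not in the whole trial. The technology tutorial before baseline and the request to keep the same equipment also reduce familiarity effects, though they do nothing about learning the tests themselves.

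A reader might infer more than the article supports:

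- **That a significant decline would also count as efficacy.** The rule is tied to Hypothesis 1, which specifies improvement. Two-sided testing of a directional hypothesis is ordinary.
- **That regression to the mean would inflate the change.** No criterion selects patients for low cognition; the telephone MMSE criterion excludes low scorers.
- **That easing of confinement would push scores up.** The article gives no dates for easing and expects the pandemic context to persist, and recruitment is spread from May 2020 to September 2021. Calendar effects are possible, but their direction is unknown.
- **That a false claim is very probable.** That depends on a retest gain the article does not give. At 0.05 the chance is 33%.

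**Conclusion.** The point holds. The stated rule for the primary hypothesis cannot show efficacy in a design where both arms exercise, and retest gain alone could satisfy it. This conclusion follows from the design and needs no numerical assumption. The size of the risk does: from 33% at a gain of 0.05 to over 99% at 0.15, given 98 completers, a change SD of 0.325 and no true benefit, and about 57% at a gain of 0.10 with a change SD of 0.46.

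The article also contradicts itself on which contrast is primary. The sample size section gives that place to the between-arm difference; the analysis section gives it to the uncontrolled change. Since this governs the trial's main conclusion, it should be corrected before the analysis.

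**What to change.** 1. Delete the sentence that makes a significant pre-to-post difference evidence of efficacy.
2. Make the randomised between-arm difference in change at 6 months the confirmatory test, in line with the Sample Size Calculation.
3. Report the 3- and 6-month changes within each arm with confidence intervals, as descriptive results, and state that they include retest and calendar effects.
4. Reword Hypothesis 1 to match, as a description of change rather than a test of efficacy.

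The cost is wording only. The sample size is unchanged, because 49 per group already gives 80% power for the between-arm contrast, and no new data are needed. The trial gives up an efficacy claim for exercise alone, which its design cannot support.
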